### The test group

3.3

The patients in the test group will undergo mechanical ventilation in the 0°prone position for 2 hours, then tilted 45° towards prone to the left for 2 hours and tilted 45° towards prone to the right for 2 hours, and returned to 0 ° prone position finally. This cycle will last for 16 hours.

### The course of treatment

3.4

The duration of treatment will be 7 days.

#### Combined treatment regulations

3.4.1

During study, it is forbidden to use PPV in other positions.

### Outcome measures

3.5

#### Primary outcome

3.5.1

The primary outcome will be the incidence of PI. Outcome indicators will be collected at day 7 of PPV.

#### Secondary outcomes

3.5.2

(1)APACHE II score: APACHE-II score includes 12 physiological scores, 1 age score, 1 Glascow scores and 5 chronic disease scores. The APACHE II score ranged from 0 to 71 points and a higher score indicated a worse severity. The APACHE II score will be evaluated at baseline, and 1 hour, 12 hour, 48 hour, 5 days and 7 days post-PI.(2)Braden Scale score: The Braden Scale score has been widely used for predicting PI risk. The Braden Scale score ranged from 6 to 23 points and a higher score indicated a high PI risk. The Braden Scale score will be evaluated at baseline, and 1 hour, 12 hour, 48 hour, 5 days, and 7 days post-PI.(3)3) Hemodynamic indexes: The hemodynamic indexes include HR, systolic blood pressure, diastolic blood pressure, central venous pressure, mean arterial pressure. The hemodynamic indexes will be evaluated at baseline, and 1  hour, 12  hour, 48  hour, 5 days, and 7 days post-PI.(4)4) Oxygenation: The Oxygenation include pH of arterial blood, oxygenation index, partial pressure of oxygen and partial pressure of carbon dioxide. The Oxygenation will be evaluated at baseline, and 1 hour, 12  hour, 48  hour, 5 days, and 7 days post-PI.

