## Abstract

**Background::**

Acute respiratory distress syndrome (ARDS) is an increasingly common acute respiratory failure that seriously threaten people's health. ARDS has a case fatality rate of up to 40%. ARDS is a serious threat to the life safety of patients and the quality of life, causing a huge economic burden to individuals, families and society. ARDS has become a large worldwide public health problem. Prone position ventilation (PPV) is an important auxiliary treatment for ARDS, which could improve oxygenation. However, PPV could cause Pressure injuries (PI) and other complications easily. We found that 45° PPV could reduce the incidence of PI, but lack of robust Evidence-based medicine evidence proving its efficacy. Therefore, we designed a randomized controlled trial to evaluate the efficacy of 45° PPV in the treatment of ARDS.

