**Methods::**

A total of 268 patients will be randomly assigned to the control group and the test group (n = 134 each) in a ratio of 1:1. The treatment period is 7 days. The primary outcome measure will be the incidence of PI. The secondary outcomes will include APACHE II score, Braden Scale score, heart rate, systolic blood pressure, diastolic blood pressure, central venous pressure, mean arterial pressure, pH of arterial blood, oxygenation index, oxygen partial pressure, and carbon dioxide partial pressure. The evaluation will be performed at baseline, 1 hour, 12 hour, 48 hour, 5days, 7days after PPPV.

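### Section 3.5.2 times all secondary outcomes from pressure injury, while the abstract times them from prone ventilation; one time zero for every randomised patient is needed

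*Protocol article*

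**What the plan says.** Section 3.5.2 defines four groups of secondary outcomes. For APACHE II it states: "The APACHE II score will be evaluated at baseline, and 1 hour, 12 hour, 48 hour, 5 days and 7 days post-PI". For the Braden scale it states: "The Braden Scale score will be evaluated at baseline, and 1 hour, 12 hour, 48 hour, 5 days, and 7 days post-PI". The items on haemodynamics and oxygenation repeat the same five post-baseline times and the same anchor. So the anchor appears four times, once per group.

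The article gives PI one meaning. The abstract introduces it in saying that "PPV could cause Pressure injuries (PI) and other complications easily", and section 3.5.1 makes it the main endpoint: "The primary outcome will be the incidence of PI. Outcome indicators will be collected at day 7 of PPV". A pressure injury already present on admission is an exclusion criterion (section 2.2.2), so a PI counted in the trial is a new event.

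The abstract lists the same secondary outcomes with a different anchor: "The evaluation will be performed at baseline, 1 hour, 12 hour, 48 hour, 5days, 7days after PPPV". The last abbreviation is not defined; I read it as PPV. Section 3.4 adds: "The duration of treatment will be 7 days". Section 3.10 plans an intention-to-treat analysis alongside a per-protocol one.

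**The concern.** The detailed methods section and the abstract give two different time zeros for the same measurements. This is not a detail that an article leaves to a fuller document: the article states the schedule, and states it in conflict with itself.

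The anchor matters because a clock that starts at the pressure injury has three defects that a clock starting at PPV does not have:

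- It is defined only for patients who have the primary event, which the intervention is meant to prevent. A comparison of arms within that subset conditions on something that happens after randomisation, and it cannot be an intention-to-treat comparison.
- It starts at a different point of treatment in each patient, so the 1-hour and 12-hour readings would not describe the early response to the position.
- Its later visits fall after the treatment period has ended.

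The article's expectation that tilted positioning may improve oxygenation rests on these outcomes. Readings taken against the wrong clock cannot be recovered afterwards. Because the anchor is the same throughout section 3.5.2, a data collector who works from that section alone would see nothing amiss.

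**Working it through.** **Inputs**

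- Assumed 7-day PI incidence: 42.7% control, 22.7% test (section 2.3).
- Alpha 0.05, two-sided (sections 2.3 and 3.10). The symbol before 0.10 in section 2.3 is lost in the text; I read it as beta, so power is 90%.
- 111 per arm before allowance for loss; 268 in total, 134 per arm (section 2.3 and abstract).
- Treatment period 7 days (section 3.4).

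**The plan's own figure.** With unpooled variance, n = (1.960 + 1.282)² × (0.427 × 0.573 + 0.227 × 0.773) / 0.200² = 10.51 × 0.4201 / 0.04 = 110.4, rounded up to 111 per arm. The stated figure reproduces. (The pooled-variance form gives 114.) It depends only on the primary outcome, so the anchor of the secondary outcomes does not touch it.

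**Who would have post-baseline readings**

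| Time zero | Control | Test | Share of patients |
|---|---|---|---|
| PPV, 111 per arm | 111 | 111 | 100% |
| PI, 111 per arm | 111 × 0.427 = 47.4 | 111 × 0.227 = 25.2 | 72.6 / 222 = 32.7% |
| PPV, 134 per arm | 134 | 134 | 100% |
| PI, 134 per arm | 134 × 0.427 = 57.2 | 134 × 0.227 = 30.4 | 87.6 / 268 = 32.7% |

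Under the PI anchor the arms stand at 42.7 / 22.7 = 1.9 to 1. That imbalance would come from the treatment effect itself.

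**Precision under the literal reading.** For a difference in means with the same per-patient SD, the ratio of standard errors is √(1/47.4 + 1/25.2) / √(2/111) = 0.2465 / 0.1342 = 1.84. The ratio is the same at 134 per arm, because both terms scale with n. It covers loss of precision only; selection bias would come on top.

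**Calendar under the literal reading.** If the injury arises t days into treatment, the last visit falls on day t + 7. That is beyond the 7-day period for any t above 0; an injury on day 5 puts it on day 12. The 5-day visit falls on day t + 5, beyond the period for any t above 2.

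**The places side by side**

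- Abstract: same outcomes, same times, counted from PPV.
- Section 3.5.1: primary outcome counted from PPV.
- Section 3.4: treatment lasts 7 days, which matches a last visit at 7 days only if the clock starts with PPV.
- Section 3.10: intention to treat, which needs a schedule that every randomised patient has.
- Section 3.5.2: counted from PI, in all four items.

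Only section 3.5.2 departs from a PPV clock.

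**The case against.** A reader might infer from section 3.5.2 that the trial will collect or analyse secondary outcomes only in patients with a pressure injury, and that the randomised comparison is therefore broken. The case against that inference is strong, and most of it stands.

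- No section limits collection or analysis of secondary outcomes to those patients. The abstract lists the same visits without that condition, and the stated analysis is by intention to treat.
- The literal reading is not a coherent plan. The article describes the Braden scale as a tool for predicting the risk of injury, so timing it only after an injury would defeat its purpose. The article also describes no recording of the hour of onset to which a 1-hour reading could be tied. A last visit on day 12 of a 7-day treatment fits a slip better than a design choice.
- The counts of 47 and 25 and the factor 1.84 therefore describe what would follow if staff obeyed the wording to the letter. They are not a forecast.
- Figure 2, which the article says holds the assessment schedule, could not be seen. It may state the right anchor.
- Only secondary outcomes are involved.

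What does not follow is that the text can stay. A probable slip that is repeated in every item of the section defining the outcomes, and that contradicts the abstract, still leaves the schedule wrong as written.

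**Conclusion.** The point holds as an internal contradiction: section 3.5.2 and the abstract give incompatible time zeros for all four groups of secondary outcomes. The probable explanation is that PI was written for PPV. The documents do not support the stronger conclusion that the trial restricts these outcomes to patients with an injury or has abandoned the randomised comparison for them.

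The size applies only if section 3.5.2 is followed literally. About one third of patients (32.7%) would then have post-baseline secondary data, split roughly 47 to 25 at 111 per arm, with a standard error about 1.84 times that of the full comparison. This assumes the planned PI rates, an unchanged SD, and readings in every patient with an injury and in no other. With PPV as the anchor, every randomised patient has a defined schedule.

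The primary outcome and the sample size do not depend on this. It should be fixed, but it does not threaten the trial's main result.

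**What to change.** Reconcile section 3.5.2 with the abstract. In items (1) to (4), replace the PI anchor with one PPV-based time zero that is the same in both arms and defined for every randomised patient. Correct the undefined abbreviation in the abstract at the same time.

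The sponsor must also say which PPV moment is meant. PPV is given in daily 16-hour periods over 7 days, and neither the abstract nor section 3.5.2 says whether the hours run from the start or the end of a session. The start of the first session is my suggestion, because it gives a single fixed origin per patient; the abstract does not say so.

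Then check that Figure 2 and the visit labels on the paper and electronic CRFs agree with the corrected text. If recruitment has begun, confirm which clock the data collectors have used.

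The cost is a wording change in four places, a correction in the abstract, and a check of the figure and forms. No change to the sample size or the primary analysis is needed.

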#### Safety outcomes

3.5.3

Other complications of PPV include unplanned extubation, catastrophic hypoxemia, pneumothorax, eye complications and intracranial hypertension. If an adverse event (AE) occurs, the investigator will record the details (including symptoms, time of occurrence, duration, examination, and results) in the form of a case record form (CRF). Serious adverse event (SAE) will be reported to the ethics committee of Guangzhou Panyu Central Hospital, and relevant rescue procedures will be started immediately.

#### Data management

3.5.4

Test data will be recorded in paper-based and electronic CRF. An independent data-monitoring committee reviewed the data every 6 months. Only investigator and monitors could access the electronic CRF. Clinicians and data analysts will not be able to access the data during the evaluation process. At the end of the trial, the database will be locked by the data management team, after which the investigator cannot modify the data. Paper and electronic documents will be kept for at least 5 years.

### Ethics

3.6

This study has been approved by the ethics committee of Guangzhou Panyu Central Hospital (ethics No.: YF2020–104-13) and registered in China clinical trial registration center on November 26, 2020. The trial strictly followed the Helsinki Declaration (2000 EDITION). Only patients with informed consent can participate in the trial.

### Dissemination

3.7

The results of this study will be disseminated through scientific conferences and per-papers. According to reasonable requirements, the readers could contact the corresponding author to obtain the data.

### Confidentiality

3.8

All personal information of the participants will be kept strictly confidential and the anonymized individual patient data will be shared on request.

### Ancillary and post-trial care

3.9

In case of injury related to this study, the subjects can obtain corresponding medical and nursing care. Meanwhile, they are entitled to compensation.

### Statistical analysis

3.10

Statistical analysis will be performed on an intention-to-treat-basis. The measurement data will be prestend

In this trial, we will conduct intention to treat analysis and protocol analysis. The measurement data will be expressed as mean ± standard deviation and the enumeration data will be expressed as in percentage. The student *t*-test will be performed for measurement data and chi square test or Fisher exact probability methods for enumeration data. All data statistics were conducted using a bilateral test, and statistical significance was set at *P* < .05. The clinical results will be analyzed by SPSS 22.0 statistical software (IBM SPSS statistics, IBM Corp, Somers, NY).

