**Conclusion::**

45° PPV may reduce the incidence of PI and improve oxygenation in patients with ARDS, which has important value in practical application

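### Section 3.10 names only the Student t-test for 11 continuous outcomes read at baseline and five later times; a baseline-adjusted longitudinal analysis would serve them better

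*Protocol article*

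**What the plan says.** The statistical analysis section (3.10) of the protocol article assigns one type of test to each type of data. For continuous data: "The student *t*-test will be performed for measurement data"; categorical data get a chi-square or Fisher exact test. One significance rule covers everything: "All data statistics were conducted using a bilateral test, and statistical significance was set at *P* < .05". The section also promises intention-to-treat and protocol analyses. It names no other method for continuous data.

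The outcomes to which the t-test applies are listed in the abstract (Methods): "The secondary outcomes will include APACHE II score, Braden Scale score, heart rate, systolic blood pressure, diastolic blood pressure, central venous pressure, mean arterial pressure", followed by arterial pH, oxygenation index, and the partial pressures of oxygen and carbon dioxide. Section 3.5.2 gives the same set, for example "The hemodynamic indexes include HR, systolic blood pressure, diastolic blood pressure, central venous pressure, mean arterial pressure". On timing the abstract says: "The evaluation will be performed at baseline, 1 hour, 12 hour, 48 hour, 5days, 7days after PPPV". Section 3.5.2 gives the same times but counts the later ones from the pressure injury (post-PI).

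The primary outcome (section 3.5.1) is the incidence of pressure injury, collected at day 7.

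**The concern.** The method named does not match the data collected. A Student t-test compares two means at one occasion. It cannot represent several readings per patient, and it does not take the baseline value as a covariate. Applied occasion by occasion, it yields many tests at an undivided 0.05 level and leaves out the information in the baseline.

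This goes beyond a detail left to an analysis plan that is not shown. The article has chosen a method, and an analysis plan that used a longitudinal model would depart from what section 3.10 says.

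What is at stake is how the secondary results can be read. The abstract's conclusion already expects that "45° PPV may reduce the incidence of PI and improve oxygenation in patients with ARDS". Oxygenation is four variables at five later times, so up to 20 contrasts could bear on that statement. Estimates would also be less precise than the collected data allow.

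**Working it through.** **The plan's own figure.** The article gives no number for the secondary outcomes. Its sample size (section 2.3) concerns the primary outcome only, and it reproduces. With 42.7% v 22.7%, two-sided alpha 0.05 and 90% power (0.10 read as beta), the unpooled formula gives (1.960 + 1.282)² × [0.427 × 0.573 + 0.227 × 0.773] / 0.20² = 110.4. This rounds up to the stated 111 per arm.

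**Number of tests.** Outcomes (abstract Methods; section 3.5.2): 2 scores + 5 hemodynamic + 4 oxygenation = 11. Post-baseline times: 1 h, 12 h, 48 h, day 5, day 7 = 5. Up to 11 × 5 = 55 contrasts; oxygenation alone, 4 × 5 = 20.

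**Chance findings with no true effect.**
- Expected number: 55 × 0.05 = 2.75, whatever the correlation. For oxygenation alone: 20 × 0.05 = 1.0.
- At least one, if all 55 were independent: 1 − 0.95^55 = 94.0%.

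Independence is not realistic here, so the 55 test statistics were also simulated. Correlation was exchangeable between times and between outcomes, with 100,000 draws per setting. The correlations are assumptions; the article gives none. Chance of at least one result with P < .05:

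| Correlation between times | Between outcomes 0 | 0.3 | 0.5 |
|---|---|---|---|
| 0.3 | 92.2% | 88.4% | 80.8% |
| 0.5 | 89.0% | 84.5% | 76.1% |
| 0.7 | 82.8% | 77.0% | 67.6% |
| 0.9 | 69.2% | 62.1% | 52.2% |

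**Precision.** Let r be the correlation between baseline and a later reading (assumed), with equal variance at both times. Relative to a raw-value t-test (variance 1), a change-score t-test has variance 2(1 − r) and baseline adjustment has 1 − r².

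| r | Raw t-test | Change-score t-test | Baseline-adjusted | Cut v raw | Cut v change score |
|---|---|---|---|---|---|
| 0.3 | 1 | 1.40 | 0.91 | 9% | 35% |
| 0.5 | 1 | 1.00 | 0.75 | 25% | 25% |
| 0.7 | 1 | 0.60 | 0.51 | 49% | 15% |

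The last column is 1 − (1 − r²)/[2(1 − r)] = (1 − r)/2. Adjustment has the smallest variance in every row.

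**After the change.** One overall comparison per outcome leaves 11 tests. The expected number of false positives is 11 × 0.05 = 0.55. The chance of at least one, if independent, is 1 − 0.95^11 = 43.1%. That is still well above 5%, which is why the secondary contrasts should also be labelled exploratory.

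**The case against.** The strongest reply is that much of the case is inference. Section 3.10 does not say that a test is run at every time, that raw values are compared, or that the baseline goes unused. A t-test on change from baseline fits the same sentence. This stands: 55 is an upper count from a plain reading, and it would be wrong to say that the plan ignores the baseline. The objection does not rescue the method, because a change-score t-test is less efficient than adjustment and leaves the number of tests the same.

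A second reply is that a key time point, a test hierarchy and missing-data rules are commonly left to an analysis plan. This also stands, and their absence from the article is not held against it. The point rests on the method and level that the article does fix.

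A reader might also infer that the day 5 and day 7 comparisons drop everyone without a reading and so compare survivors only. The article does not support that. It promises an intention-to-treat analysis, says nothing on imputation, and does not say which patients will lack readings. A weaned patient is a survivor and can still have blood pressure or APACHE II recorded.

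Finally, in a randomised trial an unadjusted t-test on complete data is unbiased; it is only less precise. That is correct and limits how serious the point is.

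**Conclusion.** The point holds as a weakness of the secondary analysis. The only method stated for continuous data does not suit repeated readings and does not adjust for the collected baseline. On a plain reading, up to 55 tests at 0.05 give 2.75 expected false positives. The chance of at least one is about 52% to 92% over the assumed correlations. The 94% figure needs independence and should not be quoted as the trial's error rate. The variance saving of 9% to 49% rests on assumed r of 0.3 to 0.7 and on comparison with raw-value tests.

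Two stronger readings are not supported. The first is that the main result is compromised: the primary outcome is one binary endpoint, tested by chi-square or Fisher, and is untouched. The second is that any single significant test would be taken as proof of better oxygenation: the abstract's sentence is a hedged expectation, and nowhere does the article say that every secondary result will be claimed as confirmatory.

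**What to change.** 1. Reconcile the time anchor first. The abstract counts the later readings from prone ventilation; section 3.5.2 counts them from the pressure injury, which gives a patient without an injury no starting point. A longitudinal model needs one time axis, defined for every patient.
2. In section 3.10, replace the t-test for the repeated continuous outcomes with one longitudinal model per outcome: arm, time, arm × time and the baseline value as covariate, with within-patient correlation modelled. SPSS, the software already named, can fit this with its MIXED procedure. The simpler alternative is ANCOVA at a single time named in advance.
3. State that secondary contrasts are exploratory and report them as estimates with 95% confidence intervals.
4. Report deaths by arm next to the day 5 and day 7 results. The article cites case fatality of up to 40%. A mixed model that assumes data are missing at random does not by itself resolve readings that cannot exist after death.

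The change needs no new patients or measurements. It costs a rewording of section 3.10 and slightly more analysis work, and there will be fewer nominally significant secondary claims.

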### Sample size

2.3

The sample size was calculated based on the incidence of 7-day PI. According to the previous literature,^[24]^ we hypothesized that the incidence of 7-day PI in the control group and the test group will be 42.7% and 22.7%, respectively. Set ɑ = 0.05 and □ = 0.10. We use PASS 15 software (PASS NCSs, LLC, USA) to calculate the size of the control group and test group, N1 = N2 = 111. Assuming that 20% of patients may be lost during follow-up, a total of 268 patients will be recruited.

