### Randomization

2.4

Patients will be randomly allocated into either to the control group and the test group according to the ratio of 1:1. The random allocation sequence listing will be generated by SPSS software operated by a third party who will not participate in the clinical study. The randomization information will be concealed until the end of the trial.

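### The primary test of 7-day pressure injury is unadjusted although baseline Braden and APACHE II are already collected: a valid test, but precision that could be had at little cost is passed up

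*Protocol article*

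**What the plan says.** All places are in the protocol article.

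- **Primary outcome (3.5.1):** "The primary outcome will be the incidence of PI. Outcome indicators will be collected at day 7 of PPV". Each patient either has a PI or does not, so this is enumeration data.
- **Test (3.10):** "chi square test or Fisher exact probability methods for enumeration data", two-sided at the 5% level. No covariate enters the stated comparison.
- **Baseline data (3.5.2):** Braden and APACHE II are both scored at baseline. On Braden the text says: "The Braden Scale score has been widely used for predicting PI risk". APACHE II is described as a measure of severity, and the text does not link it to PI.
- **Sample size (2.3):** the assumption is that "the incidence of 7-day PI in the control group and the test group will be 42.7% and 22.7%, respectively", with "Set ɑ = 0.05 and □ = 0.10". The second symbol is garbled but is evidently the type II error. The result is 111 per arm, raised to 268 in total for 20% loss.
- **Randomisation (2.4):** allocation is "according to the ratio of 1:1".

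**The concern.** The protocol names a baseline measure as a predictor of its primary outcome, plans to record it, and then leaves it out of the primary comparison. When a covariate measured before treatment predicts the outcome, a prespecified adjusted analysis normally estimates the treatment effect more precisely from the same patients. It also accounts for whatever chance difference in that covariate arises between the arms. Choosing the covariate after seeing the data would be open to the charge of selection, so the opportunity exists only if the model is fixed in advance.

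What is at stake is modest: some power and a somewhat narrower interval. The validity of the trial is not in question.

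**Working it through.** **Inputs.** Control rate 0.427 and test rate 0.227 (difference 0.200), type I error 0.05, power 0.90, 111 per arm, 20% loss and 268 recruited, i.e. 134 per arm (2.3 and abstract); two-sided testing (3.10). The R² of the baseline scores for PI is **not in the documents** and is assumed below.

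**Step 1: reproduce the plan's figure.**

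- Sum of the two variances: 0.427 × 0.573 + 0.227 × 0.773 = 0.2447 + 0.1755 = 0.4201.
- Unpooled formula: n = (1.960 + 1.282)² × 0.4201 / 0.200² = 110.4, so 111 per arm. This matches.
- Pooled formula: mean rate 0.327, and 2 × 0.327 × 0.673 = 0.4401. Then n = (1.960 × √0.4401 + 1.282 × √0.4201)² / 0.200² = 113.5, so 114 per arm, close to 111.

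The sample size is therefore that of an unadjusted comparison of two proportions, which is what 3.10 plans to carry out.

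**Step 2: unadjusted power.** On the pooled formula, power = Φ[(0.200 × √n − 1.960 × √0.4401) / √0.4201].

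- n = 111: 89.3%.
- n = 107 (134 × 0.8 = 107.2): (2.069 − 1.300) / 0.648 = 1.186, giving 88.2%.
- n = 134 (everyone analysed): 94.1%.

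On the unpooled formula, 111 and 107 give 90.2% and 89.1%.

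**Step 3: power after adjustment.** A covariate that explains a share R² of the outcome variation makes n patients per arm act like about n / (1 − R²). With n = 107 and the pooled formula:

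| Assumed R² | Effective n per arm | Power |
|---|---|---|
| 0 | 107.0 | 88.2% |
| 0.02 | 109.2 | 88.8% |
| 0.05 | 112.6 | 89.8% |
| 0.10 | 118.9 | 91.3% |
| 0.15 | 125.9 | 92.7% |

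**Step 4: check by simulation.** The formula in step 3 is an approximation for a binary outcome. Logistic regression with one normally distributed baseline covariate was therefore simulated, with 107 per arm, the same marginal rates and 4,000 runs per setting (simulation error about 0.5 points). R² here is the share of control-arm outcome variance that the covariate explains.

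| R² | Unadjusted | Adjusted |
|---|---|---|
| 0 | 88.8% | 88.7% |
| 0.055 | 89.0% | 90.1% |
| 0.122 | 88.4% | 91.9% |
| 0.171 | 87.9% | 92.5% |

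The simulation agrees with the approximation. Adjusting for a covariate with no predictive value costs practically nothing and gains nothing.

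**The case against.** **The chi-square test is not wrong.** This stands in full. The test is valid under the 1:1 randomisation, it matches the sample-size calculation, and its error rate already allows for chance imbalance at baseline. A reader might infer from the omission that the primary analysis is flawed or contradicts the rest of the protocol. It does neither.

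**The gain may be very small.** This also stands. The documents give no R², odds ratio or discrimination figure. Section 3.5.2 supports Braden in words only and does not link APACHE II to PI at all. The population is also fairly uniform: all need invasive ventilation, all are treated prone, and patients with PI at admission are excluded. Baseline risk may therefore vary little, although that is an inference.

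**The shortened sample needs the adjustment.** A reader might infer this because 268 recruited with 20% loss leaves about 107 per arm and not 111. The figures do not support it. The step from 111 to 107 costs about 1 point of power on either formula. If all 134 per arm are analysed, as intention to treat would suggest, power is above 90% without any covariate. Setting the pooled 88.2% against the stated 90% also mixes formulas, because 111 comes from the unpooled one. The allowance for loss is a separate matter with its own repair (111 / 0.8 = 138.75, so 139 per arm or 278 in total).

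**There is no stratified randomisation and no confidence interval.** A reader might count these as defects as well. An article may leave both to the full protocol or analysis plan, which are not shown. Section 3.10 does have enumeration data reported as percentages, from which a crude risk difference and its interval follow. An analysis plan might likewise add an adjusted model.

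What remains is that the article does state the primary test, that the test is unadjusted, and that a predictor named by the protocol itself is available at baseline.

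**Conclusion.** The point holds as an inexpensive improvement and not as a correction of an error. At 107 per arm the gain in power over the unadjusted 88.2% is about 0.6 points at R² 0.02, 1.6 at 0.05, 3.1 at 0.10 and 4.5 at 0.15, and essentially nil if the scores do not predict PI in these patients.

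These figures assume the planned rates of 42.7% and 22.7%, 20% loss from 134 per arm, and an R² that the documents do not supply. The case for Braden rests on the protocol's own statement. The case for APACHE II is weaker, and that score should be optional.

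**What to change.** In 3.10, before the database is locked, prespecify the primary analysis as a logistic regression of 7-day PI on treatment arm and baseline Braden score as a continuous covariate, with baseline APACHE II as an optional second covariate. Report the result as a standardised (marginal) risk difference with 95% confidence interval. That keeps the estimate on the scale of the 20-point difference used in 2.3, which an adjusted odds ratio would not. Keep the unadjusted chi-square or Fisher test as a supporting analysis.

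The cost is a reworded section and slightly more analysis work; no new data or patients are needed. Two details should be settled at the same time. One is how a missing baseline score is handled. The other is whether SPSS 22.0, the only software that 3.10 names, will produce the standardised risk difference and its interval or whether another program must be named.
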